## Abstract

Cognitive impairment in multiple sclerosis (MS) can adversely impact participation in employment, activities of daily living, and wider society. It affects 40–70% of people living with MS (pwMS). There are few effective treatments for cognitive impairment in people with MS. Neuromodulation with intermittent theta-burst stimulation (iTBS) has potential for treating cognitive impairment in pwMS. This single-centre mixed-methods feasibility randomised controlled trial (NCT04931953) will assess feasibility, acceptability, and tolerability of procedures used for applying iTBS for improving cognitive performance in pwMS. Participants will be randomised into three intervention groups with varying lengths of iTBS treatment (from 1 to 4 weeks) and a sham-control group. Quantitative data will be collected at three time points (baseline, end of intervention, and 8-week follow-up). End of the intervention semi-structured interviews will explore the views and experiences of the participants receiving the intervention, analysed using framework analysis. Quantitative and qualitative data will be synthesised to explore the impact of the iTBS intervention. Ethical approval has been received from the Health Research Authority (21/LO/0506) and recruitment started in June 2022. The results will inform the design of an RCT of the efficacy of iTBS as a therapeutic intervention for cognitive impairment in pwMS.

## Introduction

1

Multiple sclerosis (MS) is a chronic inflammatory demyelinating and neurodegenerative condition of the central nervous system [1] that affects around 140,000 people in the United Kingdom [2] and is a common cause of physical disability among working-age adults [3]. Cognitive impairment affects up to 70% of people with MS which can adversely impact participation in employment, activities of daily living, social interaction, and the individual’s potential to engage with rehabilitation [4]. There are currently few effective treatments for cognitive impairment in people with MS [5,6]. A recent expert position paper has called for the development of treatments that are based on biologically plausible mechanisms of action and that these are trialled in high-quality trials with outcome measures that are meaningful in the context of the patient’s life [7].

Interventions that can directly modulate the function of targeted brain regions have been shown to reduce the burden of symptoms in depression [8] and have potential therapeutic roles in Parkinson’s disease [9] and Alzheimer’s disease [10]. One such neuromodulation approach is repetitive transcranial magnetic stimulation (rTMS), a non-invasive procedure that applies magnetic pulses on the surface of the scalp to reach underlying brain tissue [11]. rTMS is reported as a safe and effective treatment, does not require hospital admission or anaesthesia, and is approved by the National Institute for Health and Care Research for the treatment of depression [12] and migraine [13].

Repetitive TMS can increase the excitability in the targeted cortical (and connected) brain regions. However, there has been evidence showing that high-frequency rTMS poses some side effects including seizure, headache, and neck pain. Intermittent theta-burst stimulation (iTBS) is a type of rTMS that uses short bursts of three high-frequency pulses administered with a short inter-burst interval that mimics the activity (firing rate) of specific types of neurons and reduces the administration time. iTBS potentiates plasticity of brain circuits in healthy individuals that lasts for a longer duration than the changes induced by standard rTMS protocols [14].

A recent systematic review found reported improvements in working memory and Stroop task performance in predominantly young (mean age 26 years) healthy non-cognitively impaired volunteers receiving iTBS targeting the prefrontal cortex [15]. Furthermore, comparable effects on brain physiology can be obtained by a lower dose of iTBS that lasts for a shorter duration than standard TMS as the required number of pulses gets delivered in a shorter time [16]. iTBS is shown to be as safe as the standard TMS protocol and appears to have a low incidence of adverse effects [16].

The neural circuit including the dorsolateral prefrontal cortex (DLPFC) is reported to have a role in regulating executive functions [17,18,19]. Studies have found evidence that people with MS reporting cognitive dysfunction have regional damage in the dorsolateral prefrontal circuit (e.g., striatum, globus pallidus, thalamus), including atrophied DLPFC, caudate, or thalamus [20,21,22]. In an analysis of 52 people with MS and 36 non-MS controls, we found that effective connectivity of the DLPFC to the caudate nucleus was decreased in people with MS who had impaired performance in the Paced Auditory Serial Addition Task 3-second stimulus (PASAT-3) compared to people with MS without PASAT-3 performance impairment and non-MS participants [23]. The findings highlight the DLPFC as a possible target for interventions aiming to maintain and/or improve cognitive functioning for people with MS through modulation of effective connectivity [23].

## Methods

2

### Study aim

2.1

This study will test the feasibility and acceptability of iTBS as an intervention for improving cognitive performance in people with MS. Group allocation will allow comparison of feasibility and acceptability of iTBS administration schedules of different total durations (1, 2, and 4 weeks) and assessment of the believability of the sham administration, which will inform the design of a phase III trial which will investigate the clinical- and cost-effectiveness of the treatment.

### Study design

2.2

A single-centre, mixed-methods feasibility randomised controlled trial will be conducted to compare four groups (target: 10 participants each) of iTBS administration. Participants will be randomised into one of four groups:Group 1: iTBS intervention – daily sessions for 4 days over 1 week (total 4 iTBS sessions).Group 2: iTBS intervention – daily sessions for 4 days per week over 2 weeks (total 8 iTBS sessions).Group 3: iTBS intervention – daily sessions for 4 days per week over 4 weeks (total 16iTBS sessions)Control Group 4: sham iTBS intervention – daily sessions for 4 days per week over 2 weeks (total 8 sham iTBS sessions).

Participants will complete outcome measures at three time points during the study: baseline, end of intervention (EOI) (i.e., 5 weeks after the baseline), and 8-week follow-up (i.e., 13 weeks after baseline). Participants will undergo MRI scans at baseline and EOI. We will conduct post-intervention interviews to explore the participants’ experiences of the trial, including the tolerability of the protocol, acceptability of the visit schedule, and any perceived differences in cognition.

#### Primary objective

2.2.1

The primary objective is to assess the feasibility of the trial procedures, in terms of their acceptability and tolerability for people with MS.

To address this primary objective, we will:– Assess the feasibility of recruitment, including the proportion of eligible and consenting participants.– Assess the acceptability of overall trial participation for the 1-, 2-, and 4-week groups.– Assess the tolerability of the iTBS intervention (or sham), including any side effects.– Establish the believability of sham iTBS administration.

#### Secondary objectives

2.2.2

Secondary objectives are to:– Measure changes in cognitive assessment scores by group between baseline and EOI assessments (standardised interval of 5 weeks apart), to allow comparison of effect sizes between groups.– Measure changes in cognitive assessment scores by group between EOI and 8-week follow-up assessments, to allow comparison of effect sizes between groups.– Measure changes in participant-reported effects on cognition by group between baseline, EOI, and 8-week follow-up assessments, to allow the comparison of effect sizes between groups.– Explore (at the follow-up interview) participant views on meaningful change in cognition in relation to the demands of trial participation.– Measure changes in scores for anxiety, depression, and fatigue before and after intervention, to allow comparison of effect sizes between groups.– Measure changes in the effective connectivity between left DLPFC and left caudate nucleus, to allow correlation with changes in cognition.

### Eligibility criteria

2.3

#### Inclusion criteria

2.3.1

– Clinical diagnosis of MS (any type of MS) according to the 2017 McDonald criteria [24] at least 12 months prior to baseline assessment.– Score of 55 or lower on the oral Symbol Digit Modality Test (SDMT). The SDMT threshold of 55 or lower has been chosen because it is 1 standard deviation (1sd) below the mean for young adults with high educational level, and this range includes the respective cut-offs for 1sd below mean values for other age and educational groups. This lenient cut-off value is not intended to select individuals with cognitive impairment *per se*, but to remove high-performing individuals [25]. This allows recruitment of an inclusive group of people who *may* have cognitive impairment, with a range of lower cognitive performance levels, for the purpose of this feasibility study.– Aged between 18 and 69 years.– Ability to give informed consent.– Able to commit to regular attendance in the clinic, for up to 4 times a week for 4 weeks and follow-up assessment 8 weeks after the end of trial procedures.

#### Exclusion criteria

2.3.2

– Depressive symptoms present with a score of ≥15 (the threshold for moderate depression) on the Patient Health Questionnaire-9 (PHQ-9) [26].– Medical history of, or self-reported, seizures.– Co-morbid neurological conditions (in addition to MS), e.g., brain neoplasm, cerebrovascular events, epilepsy, prior brain injury, or brain surgery.– Contraindications to MRI scanning (identified by standard MRI safety screening questionnaire).– Contraindications to TMS, including hairstyles or piercings (which cannot be altered) that would impair magnetic pulse delivery.– Frequent panic attacks which are likely to prevent regular attendance or participation in MRI/TMS procedures.– Prior TMS intervention.– Pregnancy.– MS relapse within the preceding 6 weeks.– Significant mobility problems if they are likely to preclude regular attendance in the clinic, for up to 4 times a week for 4 weeks.– Involved with any other clinical trials involving medical procedures, interventions, or treatment.– Not fluent English speaker hampering the completion of questionnaires and cognitive assessments.

### Recruitment, consent, randomisation, and blinding

2.4

Participant flow through the trial is shown in Figure 1. Participants will be recruited from the MS Clinic at the Queens Medical Centre (Nottingham, UK) and will initially be approached by a member of the patient’s usual care team. Potential participants may also contact the research team after seeing publicly available information about the study (e.g., social media, newsletters, posters). Potential participants who express an interest in the study will be sent a participant information sheet presenting information about the study and will have the opportunity to contact a member of the research team via telephone or email to ask further questions. Participants will be recruited on a “first come, first served” basis.

**Figure 1 j_med-2023-0814_fig_001:**
[figure not shown]
Trial flowchart.

Consenting procedures will be conducted by the research psychologist. Participants will be randomised after completing the consent form, and the research psychologist will be blinded to group allocation. Participants will be randomised to one of four groups in equal proportions (1:1:1:1 ratio) automatically using blocked stratified randomisation, stratified on: age group (≤40), gender (man or woman), and MS type (relapsing-remitting MS or secondary progressive or primary progressive MS). The randomisation schema was created on 9th November 2021 10:51 using *ralloc.ado* version 3.5.2 [27] in Stata version 17. The neuromodulation research fellow is notified of the group allocation via an automatic email. The research psychologist and principal investigator will remain blinded to group allocation. The two TMS operators (including the neuromodulation research fellow) administering the iTBS will not be blind to group allocation.

Participants will be blinded as to whether their iTBS intervention is real (groups 1, 2, and 3) or sham (group 4) until the end of their study participation. Although only the 2-week intervention duration has a sham comparator (group 2 = real iTBS, group 4 = sham iTBS), participants will not be made aware that the 1- and 4-week intervention durations do not have a sham comparator. Participants will be instructed not to tell the research psychologist the duration of their intervention, as this would reveal to the research psychologist that the patient received the real iTBS intervention if in the 1- or 4-week intervention groups. To standardise the assessment interval and maintain the blinded status of the research psychologist, the interval between baseline and EOI assessments will be fixed at 5 weeks, requiring commencement of the iTBS intervention to be staggered per group as per Figure 2.

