### Intervention

2.5

Depending on the group, participants will receive iTBS (or sham) intervention 4 times per week for 1, 2, or 4 weeks. Each intervention session will last around 30 min, including 20 min of iTBS. The iTBS (or sham) sessions will be delivered by two TMS operators that completed 15 h of training to deliver TMS. The sessions will be conducted in a private and quiet room located at the Clinical Research Facility of Nottingham University Hospitals. The first intervention session will be scheduled for weeks 2, 4, or 5 depending on the group. We designed this study to have, for all participants regardless of group allocation, a 5-week standardised gap between baseline assessment on week 1, administrated before any iTBS session and the EOI assessments on week 5, administrated immediately after the last iTBS session.

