#### Initial participant screening

2.6.1

Screening procedures will be conducted via telephone or videoconference by the research psychologist. The oral version of the SDMT and the PHQ-9 will be administered. Participants will be asked to complete a questionnaire regarding their demographics, MS diagnosis, and current treatments and to identify possible contraindications to MRI and TMS procedures.

Patients fulfilling the eligibility criteria will be invited to participate in the trial. Those who do not meet eligibility criteria will be excluded and thanked for their time. Reasons for ineligibility will be recorded.

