#### Baseline assessments and MRI scan

2.6.3

All participants regardless of group allocation will complete the following procedures at baseline assessment in week 1.

Participants will undergo in-person baseline cognitive and mood assessment that includes:The Brief International Cognitive Assessment for MS (BICAMS): The BICAMS was developed by an international panel to support a cognitive assessment that is brief and universal, to include tests of mental processing speed and memory. It was developed to be optimised for small centres where staff may not have formal neuropsychological training [32]. Tests included are:
The SDMT, assessing attention, working memory, and visual/spatial information processing speed [33].The California Verbal Learning Test-II, assessing verbal memory recall [34].The Brief Visuospatial Memory Test Revised, assessing visual memory [35].
Digit Span (from WAIS-IV): this test comprises two conditions, namely Digit Span Forwards (DSF) and Backwards (DSB). DSF assesses attention, encoding, and auditory processing capacity while DSB assesses working memory and executive function [36].Patient Health Questionnaire (PHQ-9) is a module of the PHQ for recording severity of depressive symptoms [26] and has been validated in primary care populations [37,38].Generalised Anxiety Disorder (GAD-7) is a brief scale to screen for generalised anxiety disorder [39].The Perceived Deficits Questionnaire (PDQ) assesses subjective cognitive dysfunction in people with MS [40]. The PDQ includes four subscales (attention/concentration, retrospective memory, prospective memory, and planning/organization).The Modified Fatigue Impact Scale (MFIS) is a self-report questionnaire exploring the effects of fatigue across physical, cognitive, and psychosocial modalities. It is a modified form of the Fatigue Impact Scale [41] and was developed following interviews with people with MS who discussed how fatigue had impacted their daily lives.The Edinburgh Handedness Inventory (EHI) assesses whether participants favour their left or right hand to inform the MRI analysis.

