Participants will have a 3T MRI scan to allow target localisation, quantification of MS lesion burden, and characterisation of brain networks and connectivity. The MRI scan will include:High-resolution T1-weighted volume, for image co-registration and segmentation;Resting-state functional MRI, for functional connectivity analysis;Fluid-attenuated inversion recovery, for MS T2 lesion quantification;Diffusion tensor imaging, for structural connectivity analysis;

The T1-weighted and resting state functional MRI will be used to estimate the iTBS intervention targets.

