#### Intervention visits

2.6.4

Two working days before the participants’ first visit, staff delivering the iTBS (or sham) intervention will ask participants if anything has changed since they were assessed which may impact their cognitive abilities, such as infection or MS relapse. If they have MS relapse or active/recent infection, they will be withdrawn from the study.

The first iTBS (active or sham) session will begin with the estimation of the RMT as detected using electromyography (EMG) to record a motor response in the contralateral abductor pollicis brevis. This is achieved by administration of single pulses of TMS to the scalp over the approximate location of the primary hand motor area of the left hemisphere, identified using the StimGuide neuronavigation system to locate the C3 position on the scalp. Slight adjustments to the position of the coil and the angle relative to the scalp surface are made by the operator to optimise stimulation of the primary hand motor area. The TMS operator delivers single TMS pulses with varying intensities guided by the adaptive Parameter Estimation by Sequential Testing [42] to estimate the participant’s RMT, defined as the minimum TMS intensity sufficient to produce a >50 μV motor‐evoked potential recoded by EMG in at least 50% of trials [43].

The localisation of the left DLPFC target will be identified using a similar target-identification methodology to previous work [23,44], using effective connectivity of the left caudate to identify the maximally connected locus in the left DLFPC.

The participant then receives the intervention according to group allocation as described above in the ‘Intervention’ section.

Following each administration, the participant is asked to report any sensations they may have experienced.

In case of missed appointments, the research team will work with the participant to reschedule the appointment, providing that participants do not have more than four consecutive days without intervention (including weekends) and that the total afforded extra time does not exceed 50% of the initial intervention schedule.

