### Data analysis plan

2.9

Data will be reported according to the CONSORT 2010 statement, extension for pilot and feasibility trials [46]. The research psychologist will perform the scoring cognitive tests and questionnaires scores and collation/tabulation of other endpoints prior to unblinded group analysis. Quantitative data will be analysed using SPSS version 24.0 [47]. We will provide descriptive statistics regarding the characteristics of the participants. Rates of consenting participants, recruitment, intervention completion, acceptability, tolerability, and adverse events will be reported by group on an intention-to-treat analysis (excluding participants who withdrew from the trial before the first iTBS administration).

Quantitative analysis will be used to evaluate the change in cognition, mood, and fatigue using the cognitive assessment and questionnaires. Where appropriate, parametric or non-parametric statistics will be used to estimate effect sizes and perform between-group comparisons to inform power and sample size calculations for a potential future phase III trial.

Qualitative data (post-intervention interviews) will be analysed using framework analysis [48–51]. These will be audio-recorded and transcribed verbatim by the research psychologist. The interview transcripts will be mapped onto a predefined framework. An analytical framework will be developed according to the interview schedule which will map onto the aims of the qualitative study. The researcher will read the transcripts to get familiar with the content of the interview. Subsequent analysis will be conducted on NVivo software [52]. This process will follow Gale et al.’s guide to framework analysis [48]. Following the initial coding of the first transcript, two researchers will meet to discuss the codes and to check whether the coding is consistent and comprehensive. Disagreements will be resolved through discussion together or with a third member of the study team to prevent bias. Once all the coding is completed, the researcher will enter these data onto the framework matrix and determine the fit of the data to this matrix. Any new data that does not fit the matrix will be considered again to see whether a new thematic structure is needed to include such data.

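### Randomisation is tied to the consent form, not to a completed baseline visit and MRI, so early losses can fall after allocation and then leave the analysis set

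*Protocol article*

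**What the plan says.** Eligibility is settled at a telephone or video screen, which includes questions on MRI and TMS contraindications. After that, "Patients fulfilling the eligibility criteria will be invited to participate in the trial" (section 2.6.1). The only event to which section 2.4 ties randomisation is consent: "Participants will be randomised after completing the consent form, and the research psychologist will be blinded to group allocation". An automatic email then tells the neuromodulation research fellow the allocation.

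Section 2.6.3 describes the baseline tests and the 3T scan: "All participants regardless of group allocation will complete the following procedures at baseline assessment in week 1". The scan is needed for treatment: "The T1-weighted and resting state functional MRI will be used to estimate the iTBS intervention targets". Targeting appears under the intervention visits in section 2.6.4: "The localisation of the left DLPFC target will be identified using a similar target-identification methodology to previous work".

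On timing, section 2.5 says: "The first intervention session will be scheduled for weeks 2, 4, or 5 depending on the group". Two working days before the first visit, participants are asked about relapse and infection, and section 2.6.4 says: "If they have MS relapse or active/recent infection, they will be withdrawn from the study".

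Section 2.9 reports consent, recruitment, completion, acceptability, tolerability and adverse-event rates by group on what it calls an intention-to-treat basis, "excluding participants who withdrew from the trial before the first iTBS administration".

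**The concern.** Remote screening can ask about contraindications, but it cannot show whether a person will get through the scan. That is learned in week 1. If allocation follows directly from consent, a failed scan or a change of mind around baseline becomes a post-randomisation loss, although it has nothing to do with the allocated schedule. It uses one of about 10 places in a group and a slot in a stratified block.

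The exclusion in section 2.9 then takes the same person out of the reported rates. Completion of the visit schedule is an endpoint for the primary objective (Table 1), so the denominator matters. A phase III team would want to see two things separately: how many consenting people never reach a treatable state, and how many allocated people fail to complete. The current arrangement mixes the first into the second and then drops part of it.

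**Working it through.** **1. The plan's own figure.** Four groups of up to 10: 4 × 10 = 40, as stated in section 2.8. This is a pilot-size rule; no allowance for losses is stated.

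**2. Order of events in the text.** Screening (2.6.1), consent and then randomisation (2.4), baseline tests and MRI in week 1 (2.6.3), targeting (2.6.4), first session (2.5). The step from randomisation to baseline is inferred: section 2.4 places randomisation after consent, and section 2.6.3 speaks of group allocation when describing baseline. No sentence says outright which comes first.

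**3. When allocation is needed.** The end-of-intervention assessment is in week 5, directly after the last session. Counting back by treatment duration:
- group 3 (4 weeks): 5 − 4 + 1 = week 2
- groups 2 and 4 (2 weeks): 5 − 2 + 1 = week 4
- group 1 (1 week): 5 − 1 + 1 = week 5

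This matches the weeks 2, 4 or 5 in section 2.5. No group needs its allocation before the week-1 procedures are done.

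**4. Losses that later randomisation could move ahead of allocation.** Section 2.12 reports 24 recruited. Taking recruited as randomised, at most 40 − 24 = 16 remain. The rate of loss between consent and completed MRI is not given, so the rates below are assumptions.

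| Assumed loss | Whole design of 40 | Remaining 16 |
|---|---|---|
| 0% | 0 | 0 |
| 5% | 40 × 0.05 = 2 | 16 × 0.05 = 0.8 |
| 10% | 40 × 0.10 = 4 | 16 × 0.10 = 1.6 |

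Over the full 40, the chance that at least one group of 10 loses two or more is 1 − [P(Binomial(10, m) ≤ 1)]⁴. This is 0.30 at m = 0.05 and 0.71 at m = 0.10.

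**5. Losses that it would not move.** From week 1 to the first session the wait w is about 1 week in group 3, 3 weeks in groups 2 and 4, and 4 weeks in group 1. With an assumed weekly loss h, the expected loss per group of 10 is 10 × [1 − (1 − h)^w].

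| h per week | Group 3 | Groups 2 and 4, each | Group 1 | Total of 40 |
|---|---|---|---|---|
| 1% | 0.10 | 0.30 | 0.39 | 1.1 |
| 2% | 0.20 | 0.59 | 0.78 | 2.2 |
| 5% | 0.50 | 1.43 | 1.85 | 5.2 |

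Group 1 loses nearly four times as many as group 3 (0.39/0.10 = 3.9; 1.85/0.50 = 3.7). These losses depend on the allocated schedule, whenever randomisation takes place.

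**6. Effect of the section 2.9 exclusion.** Suppose 32 of 40 randomised participants complete and 4 of the other 8 withdrew before a first session. All randomised: 32/40 = 80% (exact 95% CI 64% to 91%). After the exclusion: 32/36 = 89% (74% to 97%). The counts are invented to show the direction and possible size.

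**The case against.** The strongest reply is that section 2.4 sets only an earliest time. Randomisation after consent is compatible with randomisation after baseline, and the wording in section 2.6.3 may mean no more than that all groups share one schedule. Figure 1 may show the order. This stands as a limit: a reader might infer that the protocol states randomisation before baseline, and it does not. It is also true that nothing in the text makes baseline or MRI a condition of allocation.

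Second, the avoidable loss may be small. Contraindications, and panic attacks likely to prevent scanning, are screened out. Baseline is not an eligibility gate, and the text has no criterion for a scan that yields no usable target. The recruitment figures in section 2.12 do not report losses before the first session. This too stands: the size is assumed, not documented.

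Third, the one stated withdrawal rule before treatment, for relapse or infection, acts after the allocation-dependent wait, so later randomisation would not prevent those exclusions. Keeping all randomised participants in the denominator would undo much of the harm. That is correct, and it is why the fix has two parts.

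Fourth, the CONSORT pilot extension and the exit interviews mean that early losses need not be hidden. They help with disclosure, but they do not change the denominator set in section 2.9.

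**Conclusion.** The point holds in a limited form, at minor to moderate weight. As written, randomisation is tied to consent without any requirement that baseline and MRI be complete, and section 2.9 removes those who withdraw before a first session from a set it calls intention-to-treat. Randomising at the end of week 1 is feasible on the trial's own schedule and would keep scan failures and early withdrawals out of the randomised comparison.

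The gain is modest: about 1 to 2 of the remaining 16 participants at an assumed 5% to 10%, and none if the true rate is near zero. This rests on the inferred order, on reading recruited as randomised, and on treating someone who cannot be scanned as a withdrawal before the first session.

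Two stronger conclusions are tempting. One is that 2 to 4 of 40 participants will be lost, with a 30% to 71% chance that some group loses two or more. The arithmetic is right, but the rates are assumed and most participants are already recruited. The other is that later randomisation would repair the intention-to-treat set. It would not, because losses in the wait of about 1 to 4 weeks remain and can differ by group.

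**What to change.** 1. **Section 2.4, for participants still to be recruited.** State that randomisation and the allocation email are triggered once the week-1 baseline assessment and MRI are complete. If this is already the practice, say so; no further change to section 2.4 is then needed.
2. **Feasibility reporting.** Report the number lost between consent and randomisation, with reasons, as feasibility data.
3. **Section 2.9.** Report by-group rates with all randomised participants in the denominator, and show withdrawals before the first session by group and reason. If the reduced set is also reported, label it modified intention-to-treat.

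**Cost.** Items 1 and 2 need a changed trigger and a sentence or two of text; item 3 is a change of wording and tabulation. There are two real downsides. The group starting in week 2 gets less notice for booking, and the check two working days before the first visit shortens it further. The trial would also have two randomisation points, one for those already recruited and one for the rest. The report should state this and give the number randomised under each.
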